## Materials and methods

### Conceptual framework

There is a strong association between poverty and poor mental health in young people [17, 18]. Psychiatric disorders in youth are often associated with social problems such as school failure or delinquency, which increase the risk of poverty and other adverse outcomes into adulthood [3, 5]. Furthermore, mental health support is inequitably distributed, so that people living in poverty and those facing other vulnerabilities are at higher risk [5]. Therefore, youth living in LMICs have increased vulnerability to mental illness and associated high mortality rates due to their social and environmental situations [11, 19].

Economic hardship can affect mental health, increase stress, and decrease self-esteem [20]. Economic stressors have been estimated to account for 24% of suicide occurrence [21]. Income inequality is associated with increased suicide rates for both men and women, mechanisms by which this association exists include limited access to resources and increased sense of injustice for not achieving as much economic success as other people [21]. Some studies indicate that poverty is more frustrating in more unequal communities, possibly because individuals become frustrated when comparing themselves to others [22]. In Brazil, income inequality has been associated with higher suicide rates [8] Poverty can increase predisposition to mental illness such as alcohol abuse/dependence and depression in families [22]. It has been shown that cash transfer programs can improve general mental health [23] and increase hope and optimism [24]. It can also reduce factors that are associated with suicide, such as exposure to violence and impulsivity. Factors that can be tested in the current project by accessing notifications and hospitalizations related to those causes.

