Several drivers and mechanisms have been hypothesized to underlie the process of the association between cash transfer and better mental health outcomes, and there is also a bidirectional and intergenerational component. Haushofer and Shapiro (2016) have shown that the receipt of a fixed monthly income resulted in a short-term increase in self-reported welfare among beneficiaries in Kenya [25]. A review summarized the causal evidence and mechanisms for the relationship between poverty and common mental illnesses [5]. Poverty can increase exposure to factors that lead to poor mental health, such as economic tension and family violence. Poverty may also be a barrier to accessing goods, resources and services (which can make it impossible to satisfy even basic needs), contributing to the sense of social injustice generated from inequities in access [22]. Therefore, cash transfers could increase the welfare of beneficiaries by providing greater financial stability, as well as improving family members mental health.

We hypothesize that a socioeconomic intervention, Bolsa Família Program (BFP), could be associated with better mental health outcomes among youth, by mitigating some social drivers for poor mental health, such as exposure to violence [14]. Similarly, the possible BFP effect could be mediated by the reduction of important risk factors for mental illness among youth, parents’ mental illness and school dropout because of child labor. All testable variables in our datasets. By decreasing impulsivity, measured by hospitalizations from injuries, BFP could decrease attempted suicides and suicide cases among youth (Fig 1).

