**Fig 2 pone.0272481.g002:**
[figure not shown]
Flowchart of non-beneficiary (non-BFP) and beneficiary of the Bolsa Familia Program (BFP) to test the association between BFP and youth mental health-related hospitalizations and suicide.

**Table 1 pone.0272481.t001:** Summary of the dataset’s description, from 2001 to 2018.

Dataset	Description	Sample	Variables of interest
The 100 Million Brazilian Cohort Baseline^70,73^	It was built from socioeconomic and demographic information of individuals applying for social benefits in Cadastro Unico (CadÚnico). CadÚnico is an extensive questionnaire with information on the household and on each individual.	114 million Brazilian cohort, including 66,079,181 Bolsa Familia Program beneficiaries and 47,928,524 non-beneficiaries. Among them 41,764,126, youth aged from 5–24 years old in the day of registration.	Demographic and socioeconomic variables (sex, age, ethnicity, education, work), conditions of the household (type of residence, material of household, household density, household supply, garbage destination etc), Health Care utilization, Institutional and community support (participation in groups, access to Social Assistance Reference Center, etc.) and Brazilian government social protection programs (BFP, etc).
Mortality Information System (SIM)^74,75,72^	The national system aimed to collect information on all deaths in Brazil death certificates. All deaths are recorded using a national standardized form and causes of death are registered according to the updated International Classification of Diseases CID-10.	All mortality cause (n = 21,313,290), including suicide (n = 181,527).	Demographic and socioeconomic variables (sex, age, ethnicity, education, work), place the death took place and primary and secondaries causes of death.
Hospital Information System (SIHSUS)^1^	All hospitalizations admissions financed by the Brazilian National Health System are recorded in this system. It includes about 80% of the Brazilian populations, approximately 150 million people	Hospitalizations from mental illness 5,478,980, including: 1,698,663 from alcohol and substance use-related disorders; 1,952,605 from schizophrenia; 832,974 due mood disorders, etc.	Identification and qualification of the patient, procedures, examinations, and medical acts performed, diagnosis, reasons for discharge, amounts due etc.

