We will apply methods from the SEM group, to specify and test the paths laid out in Fig 1. SEM will be used to fit models to the specifications in Fig 1 to allow a judgement on which models best fit our data, therefore allowing the identification of the model, which might be the closest to the causal paths underlying the relationship between exposure and outcome, including potential confounders. Estimation is performed either by Maximum Likelihood. Besides identification of the best fitting models, SEM allows detailing the relationship between indicators (variables) included in the models. After deciding which models are optimal, the particular coefficient estimates are calculated, which can be of fundamental importance to the identification of the intermediate nodes that have the highest influence on the outcome, or which act as mediators or moderators. Mediators are useful representations of confounders, and as long as the path coefficients are calculated, one can precisely estimate the effects resulting from the mediator.

Aim 4: Investigate early life exposures, intergenerational aspects, and to forecast scenarios in Brazil until 2030 using microsimulation models.

Finally, to match this aim we will examine: timing of the intervention in the life course, e.g., if cash transfer delivered earlier in life (e.g., in 2004 when an adolescent was 14 years old) will be associated with lower mental health-related hospitalizations and lower suicide rates 10 years later (when the same adolescent will be 24 years old); and whether mental health-related problems such as suicidality, post-traumatic stress disorder (PTSD), violent behavior passes over to second generations; and, furthermore to forecast scenarios of mental health-related hospitalizations and suicide rates using microsimulation models. This will leverage the results from previous objectives and compare the impact of different BFP implementations on mental health-related hospitalizations and suicide in Brazil until 2030.

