Some limitations must be considered. The use of proxy in one of the four mechanisms proposed, physical injuries for impulsivity, can be a possible limitation in the analysis of mechanisms. However, assessment of impulsiveness and aggression in studies of risk factors for suicidal behavior, often depend on information from proxy informants, have been evaluated as robust [42]. Since both will be controlled by health care access, it is unlikely to have major differences between the group exposed and non-exposed. Quality of administrative data could also be challenging in these studies. Problems with quality can be related to problems with data collection and completeness of the data. However, most of the variables chosen for this project have less than 1% missing data. Most data that will be used for this proposal comes from CadÚnico that tend to be filled with precision due to the legal consequences on the beneficiaries. The forms are filled by trained interviewers, and missing information could result in not participating in the cash transfer program.

The large-scale data set will allow us to investigate comprehensively and in subpopulations the effects of BFP on youth mental health, as well test mechanisms of this effect. The use of these databases will allow exploring mental health outcomes with a high level of statistical power. The databases used in this study have national coverage, low under-registration, and some have already documented reliability. Therefore, this study will provide a comprehensive and representative analysis of the poor and extremely poor Brazilian population and reinforce the adequacy of these bases for epidemiological investigations. Results from this innovative project are expected to inform national efforts to prevent mental illnesses among youth from low-income communities in Brazil through the scale-up of economic interventions; our findings may also be relevant to other comparable middle income countries experiencing challenges, such as those resulting from the economic consequences of the COVID-19 pandemic, to address the burden of mental health problems among youth and reducing mental health disparities.

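### Aim 2 takes the best-fitting structural equation model as a guide to causal paths; fit cannot tell a mediator from a consequence of the outcome or from a confounder, and no time order is stated in its place

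*Protocol article*

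**What the plan says.** In the Analytic strategy, Aims 2 and 3 test BFP effects on possible pathway variables by regression discontinuity and propensity score matching, then fit structural equation models by maximum likelihood. The selection rule is: "SEM will be used to fit models to the specifications in Fig 1 to allow a judgement on which models best fit our data". The model so chosen is described as one "which might be the closest to the causal paths underlying the relationship between exposure and outcome, including potential confounders". Its coefficients are then used to decide which intermediate nodes act as mediators or moderators. The same paragraph adds: "Mediators are useful representations of confounders".

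The Conceptual framework names four mechanisms: parental mental illness and family separation, school retention, exposure to violence, and impulsivity. Of the drivers in that section it says: "All testable variables in our datasets". It also says that "there is also a bidirectional and intergenerational component", and that "Psychiatric disorders in youth are often associated with social problems such as school failure or delinquency".

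Impulsivity is measured by hospital admissions for injury (Conceptual framework; Discussion). Physical injuries are also outcome (G) in the Aim 1 list. In Table 1, the individual education field for living cohort members stands in the row "The 100 Million Brazilian Cohort Baseline". No school attendance or retention variable is named.

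**The concern.** A mediator must follow the exposure and precede the outcome. The Aim 2 text puts goodness of fit where that order should stand. If a youth becomes ill and then leaves school, or a parent is admitted after the youth's suicide attempt, the two events are associated. A model with an arrow from school or parent to youth illness can fit that association as well as one with the arrow reversed. The same holds for a factor that was present before BFP and influenced both receipt and illness: that is a confounder.

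At stake is which mechanisms Aim 2 names. Testing the four mechanisms is one of the study's stated aims, and the article promises answers about how such programs prevent mental illness. A large cohort does not help. The Discussion says "The use of these databases will allow exploring mental health outcomes with a high level of statistical power", but more data only estimate the wrong path more precisely.

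**Working it through.** The protocol gives no figure for the mechanism tests, so there is none to reproduce. The check has three parts.

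**1. Can fit identify direction?** Let X be BFP, Y the outcome and M the candidate mediator. Assume a truth without mediation: Y = cX + e and M = bY + u, with unit error variances. Fit the mediation model (X to M, M to Y, X to Y) to such data:

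- M on X has slope bc.
- Y on M given X has slope b/(1 + b²).
- The apparent indirect effect is b²c/(1 + b²). The total effect is c, so the apparent mediated share is b²/(1 + b²).

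For b = 0.2 the share is 0.04/1.04 = 3.8%; for b = 0.4 it is 0.16/1.16 = 13.8%. The true share is 0% in both cases. One simulated run gave 4.0% and 14.8%, which differ from the formula by sampling error. It used one million records, c = −0.2, and 66,079,181/(66,079,181 + 47,928,524) = 58.0% exposed (Table 1 counts). The maximised log-likelihoods of the true and the reversed model differed by less than 1e-9.

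The reason is that both three-variable models are saturated and reproduce the same covariances. A model with M as a common cause of X and Y is saturated too, so fit cannot separate mediator from confounder there either.

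**2. Does dating the events matter, and by how much?** All inputs here are assumptions. Follow-up is 10 years. The yearly outcome hazard is 0.02 without BFP and 0.016 with it. The mediator hazard is 0.01, unaffected by BFP, and multiplied by k once the outcome has occurred. There is no true mediation. The mediated share is (BFP effect on M) × (slope of Y on M given BFP) / (BFP effect on Y), on the risk-difference scale.

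For k = 4 and outcome hazard h, P(no M) = exp(−10h − 0.1) + ∫ h·exp(−ht)·exp(−0.01t − 0.04(10 − t)) dt over 0 to 10.

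- h = 0.02: 0.7408 + 0.1410 = 0.8818, so P(M) = 0.1182.
- h = 0.016: 0.7711 + 0.1151 = 0.8862, so P(M) = 0.1138.
- The spurious risk ratio is 0.1138/0.1182 = 0.96.
- The effect on M is −0.0044, the effect on Y is 0.1479 − 0.1813 = −0.0334, and the pooled slope of Y on M is 0.168. The share is 0.0044 × 0.168/0.0334 = 2.2%.

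| k | Spurious risk ratio, BFP to M: simulated (exact) | Spurious mediated share: simulated (exact) | With time order imposed |
|---|---|---|---|
| 2 | 0.99 (0.98) | 0.3% (0.3%) | ratio 1.00, share 0.0% |
| 4 | 0.96 (0.96) | 2.4% (2.2%) | ratio 1.00, share 0.0% |
| 10 | 0.92 (0.93) | 11.7% (11.1%) | ratio 1.00, share 0.0% |

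The simulation had four million records. The last column takes the mediator from years 0 to 5 and the outcome after year 5.

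**3. Does another part of the protocol supply the order?**

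- Matching (Aim 1, used again in Aim 2) is on pre-treatment characteristics, including previous psychiatric hospitalization and educational level. That protects part of the BFP-to-mediator step, but not the mediator-to-outcome step.
- Longitudinal models are proposed under Aim 4 for its own sub-objectives only.
- The Study innovation section states an intention to examine lagged effects, but does not tie it to the four mechanisms.
- Hospital, notification and death records are event records. Order could therefore be imposed for parental admission, violence and injury, but the Aim 2 text does not impose it.

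**The case against.** The strongest reply is that direction is set in advance. The models follow Fig 1, whose caption describes pathways from BFP to outcomes, and nothing shows that reversed arrows are among the candidates. The causal wording is hedged. This is also a condensed article, so exact windows and index dates may stand in a fuller plan. All of this is fair, and the absence of window lengths is no finding. In larger, unsaturated models fit can reject some directions. What remains is the rule the text does state: fit as the guide to causal paths, and mediators read from coefficients. Fig 1 is not shown to us, and in any case arrows do not set the dates of measurement.

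Three stronger readings are tempting and not supported:

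- A reader might infer that misordered events will be counted as pathways. No text says so; they are only not excluded.
- A reader might infer that schooling is known only at registration, so that every value precedes the first payment. That rests on a row label in Table 1. Elsewhere the article claims 18 years of socioeconomic data, individual-specific trends in socioeconomic variables, and income instability as a covariate, all of which suggest repeated records.
- A reader might infer that half of the youths with both events have the mediator last. That holds only for independent, identically distributed dates, and independent events create no spurious mediation. With suicide as the outcome, the youth's own mediators cannot come afterwards at all.

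**Conclusion.** The point holds in this limited form. As written, Aim 2 lets goodness of fit guide the causal reading and blurs mediator with confounder, in a setting that the article itself calls bidirectional and where one event type, injury admission, serves as both mediator and outcome. The equal-likelihood result is exact for the linear three-variable case; how far it carries over depends on the Fig 1 models, which are not shown.

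The size of any bias in this study is unknown. The 0.3% to 11.7% range shows only that it can be negligible or material depending on how strongly illness raises later mediator events, and that the stated method would not reveal which. The point concerns the mechanism claims alone. It does not undermine the estimated total effect of BFP and does not make Aim 2 unworkable. It calls for a clarification of the protocol, to be made before the mechanism models are fitted.

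**What to change.** In Aim 2:

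1. Remove best fit as the criterion for causal direction. Fit may still be reported as a check on a model whose direction was specified beforehand.
2. Delete the sentence that treats mediators as representations of confounders.
3. State that a mediator event counts only if dated after BFP start (or the matched index date for non-beneficiaries) and before the outcome. The investigators should choose the window length. Apply it as a common window or as a time-updated mediator, since otherwise youths with early outcomes have less time in which a mediator event can be recorded.
4. For injury admissions, state which role each event plays in a given model.
5. For school retention, name a measure recorded after BFP start, and do not use the registration value as the mediator. Educational level is also a matching variable, so matching on that value would remove the contrast the mechanism needs.

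The change is to wording and needs no new data for the three mechanisms with event records. The cost is that outcomes before or during the mediator period drop out of the mechanism analysis, which lowers its precision. With a common window, the analysis also conditions on youths being outcome-free at its end, which should be stated as a limitation.

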Preventing mental illness earlier during development could decrease subsequent mental health-related hospitalizations and suicide attempts. However, prevention poses a tough challenge, as these outcomes are usually the final stage of a series of small breakdowns that happen at several levels in the life course. Considering the multi-causality of the phenomenon, it is important to investigate several social drivers, risks, and protective factors at the individual and contextual level. Poverty, gender and racial inequality are associated with increased mental illness [6] and suicide [7, 8]. This might be explained by increased stress, family difficulties, alcoholism, impulsivity, violence and parental mental illnesses among the poor [3, 9–11]. However, those mechanisms are yet to be fully understood and tested, especially among youth in a LMIC setting.

Brazil has one of the largest mental health-related hospitalizations among youth, and suicide is the third most common reason for death due to external causes, and alarmingly both have increased over the last 13 years. The World Health Organisation (WHO) recommends that suicide prevention should be prioritized on the global public health agenda [12]. However, it remains unclear what interventions are best suited for targeting youth at a population level and what preventive interventions delivered earlier in life have a long-term effect on preventing mental health-related hospitalizations and suicide.

The Brazilian government introduced the Bolsa Familia Programme (BFP) in 2003 [13] to promote social inclusion and strengthen human capital among the poorest. Poverty alleviation programs could influence mental illness by diverse pathways [3, 5, 9] through decreasing income inequalities or by reducing socioeconomic hardship through increased family income, which might result in stress reduction, less family disruption, or decreased alcohol consumption [14]. Therefore, we might expect government poverty alleviation programs such as BFP to have an impact. However, whether this Brazilian government program has impacted, and knowledge of the pathways and mechanism of its impact, on youth mental illness and suicide remains unknown.

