Our data of over half of the Brazilian population will help understand both (observationally) the association of multiple factors on both mental illness and suicide, and the impact of interventions targeting some of these factors. Within each broad analysis, we will explore pathways, mechanisms and interactions/moderators. This is especially important in LMICs, such as Brazil, where implementing preventative measures may be more challenging as a result of cultural and socioeconomic factors, limited resources, as also in large continental countries because of size and distribution of the population [15]. This study’s aims are as follows:
To use large national datasets to evaluate the effect of a broad range of social drivers and of a social-economic intervention on youth mental health,To test four mechanisms and pathways (reducing parental mental illness; increasing school retention; reducing exposure to violence; decreasing impulsivity) of the social-economic intervention on reducing mental illness among youth,To evaluate whether equity is a moderator of the effectiveness of the cash transfer program, e.g., whether the Brazilian cash transfer program improves the lives of the most vulnerable subgroups (with lower income, black population, and women) compared to less vulnerable groups, thereby reducing mental health disparities, andInvestigate early life exposures, intergenerational aspects, and to forecast the impact of socioeconomic changes and cash transfers mitigation effects in Brazil until 2030 using microsimulation models, also modelling the impact of the current COVID-19 related economic recession.

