**Aim 2: To test four mechanisms and pathways of the social-economic intervention on reducing mental illness among youth; and Aim 3: To evaluate whether equity was a moderator of the effectiveness of the cash transfer program**, **e.g., whether the Brazilian cash transfer program improved the lives of most vulnerable subgroups (with lower income, black population, and women) compared to less vulnerable groups reducing mental health disparities.**

We will evaluate whether BFP program affects youth mental health through improving social drivers by running Regression Discontinuity Design (RDD) and Propensity Score Matching (PSM), and Structural Equation Modelling (SEM) for each of them and the outcomes. Such strategies allow us to examine the pathways by testing the impact of the intervention on variables that might be on the pathway of the relation between BFP and mental health outcomes. We hypothesize that BFP has an effect on reducing mental health-related hospitalizations and suicide among youth because it also affects their social drivers. Stratified analyses by municipality size, regions, states, and levels of Human Development Index (HDI) will also be performed.

We will include a set of covariates recognized as social drivers of mental illness for youth at the individual level such as income, income instability, unemployment, isolation and at the contextual level, variables from the municipalities where the youth live, such as population, fertility, mortality, migration, housing characteristics, characteristics of the neighbourhood, municipal income, labour, economic inequality (Gini index), Human Development Index (HDI), proportion of poor people and municipal coverage of the community mental health center and number of mental health professionals in the same municipality. We will also evaluate whether equity was a moderator of the effectiveness of the cash transfer program, e.g., whether the Brazilian cash transfer program improved the lives of most vulnerable subgroups compared to less vulnerable groups, thereby reducing mental health disparities. Therefore, we will repeat the analysis stratifying by subgroups with diverse ranges of income level, black compared with the white population, and female compared to male.

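### Aim 2 describes mediators as representations of confounders and lists social drivers as covariates without fixing their timing relative to BFP entry

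*Protocol article*

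**What the plan says.** All of this is in the Protocol article.

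- **Mechanisms.** The Background names four routes to be tested: "reducing parental mental illness; increasing school retention; reducing exposure to violence; decreasing impulsivity". It also describes a broader route, "reducing socioeconomic hardship through increased family income".
- **Hypothesis for Aims 2 and 3** (Analytic strategy): "We hypothesize that BFP has an effect on reducing mental health-related hospitalizations and suicide among youth because it also affects their social drivers".
- **Covariates for the same analyses** (Analytic strategy, Aims 2 and 3): "covariates recognized as social drivers of mental illness for youth at the individual level such as income, income instability, unemployment, isolation", followed by a list of municipal variables. No measurement time is given.
- **Structural equation modelling** (Analytic strategy, Aims 2 and 3). Models are fitted to the paths of Fig 1, and the best-fitting ones are kept, "allowing the identification of the model, which might be the closest to the causal paths underlying the relationship between exposure and outcome". Coefficients are then used to say which intermediate nodes act as mediators or moderators. The paragraph closes with the claim "Mediators are useful representations of confounders, and as long as the path coefficients are calculated, one can precisely estimate the effects" that come from the mediator.
- **Timing elsewhere.** Under Aim 1 the article defines a propensity score from characteristics that precede treatment. It states the identifying assumptions of matching and of regression discontinuity. It states none for mediation.

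**The concern.** There are two linked problems, and only the second depends on timing.

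First, the closing sentence on structural equation modelling is a methodological error. In a total-effect analysis a confounder must be adjusted for and a mediator must not be. A plan that treats one as standing for the other gives the analyst no rule for the choice. The sentence also says that computing path coefficients is sufficient for a precise estimate. It is not: if an unmeasured factor, such as shared family liability, affects both the mechanism and the outcome, a mechanism with no effect can show a clear path. In a cohort this large, such a bias would come with a narrow interval.

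Second, the social drivers have two roles in the same analyses: the hypothesised route of the BFP effect, and covariates. Income is the clearest overlap, since the Background names higher family income as part of the route. If the values used are recorded after BFP entry, adjustment removes part of the effect under study. At stake are the Aim 2 conclusions about which mechanisms matter and how much of the effect they carry.

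**Working it through.** The protocol states no effect size, power or mediated proportion for this analysis, so there is no figure to reproduce. The check sets the texts side by side and then illustrates the consequence with assumed coefficients.

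**1. Roles given to the variables**

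| Variable | Role as route of the BFP effect | In the Aim 2/3 covariate list | Timing stated |
|---|---|---|---|
| Income | Yes (Background) | Yes | No |
| Income instability, unemployment, isolation | As social drivers, by the hypothesis | Yes | No |
| The four named mechanisms | Yes (Background) | No | No |

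The overlap therefore concerns the social drivers and not the four named mechanisms.

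**2. Effect of timing (linear illustration, all coefficients assumed)**

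Let B be BFP, I0 the driver before entry, I1 the driver after entry, M a mechanism, Y the outcome and U an unmeasured cause of I1 and Y. Errors and U have variance 1.

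- I1 = 0.7·I0 + g·B + u·U + error
- M = -0.3·B - 0.4·I1 + error
- Y = -0.1·B + 0.5·M - 0.2·I1 + u·U + error

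True total effect: -0.1 + 0.5(-0.3 - 0.4g) - 0.2g = -0.25 - 0.4g.

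True indirect effect through M: 0.5(-0.3 - 0.4g) = -0.15 - 0.2g.

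Adjusting for I1 as well as I0:

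- Total with u = 0: -0.1 + 0.5(-0.3) = -0.25, whatever g is.
- Total with u = 0.5: conditioning on I1 ties B to U, which adds -g·u²/(1 + u²) = -0.2g. The result is -0.25 - 0.2g.
- Indirect effect: (-0.3)(0.5) = -0.15, whatever g is.

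| g | True total | Total, I0 only | Total, I0 and I1 (u = 0; u = 0.5) | True indirect | Indirect, I0 and I1 |
|---|---|---|---|---|---|
| 0.2 | -0.33 | -0.33 | -0.25; -0.29 | -0.19 | -0.15 |
| 0.5 | -0.45 | -0.45 | -0.25; -0.35 | -0.25 | -0.15 |
| 0.8 | -0.57 | -0.57 | -0.25; -0.41 | -0.31 | -0.15 |

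Covariates from before entry recover the total effect, but they do not by themselves secure the indirect effect. With I0 only and u = 0, the fitted M-to-Y slope is 0.5 + 0.2·0.4/(0.4² + 1) = 0.569. The product (-0.3 - 0.4g)·0.569 is then -0.22, -0.28 and -0.35, against true values of -0.19, -0.25 and -0.31. The excess arises because I1 is a mediator-outcome confounder that BFP changes. With u = 0.5 the two biases in that slope happen to cancel (+0.083 and -0.083). A simulation of 1,000,000 records per setting agreed with all these values to within 0.004.

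**3. Unmeasured mediator-outcome confounding (assumed coefficients)**

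Let the true mediator-to-outcome path be 0, and let U have coefficient c on the mediator and d on the outcome. With unit error variance the mediator has variance 1 + c² given BFP, and the false path is cd/(1 + c²). If the mediator is scaled to variance 1 with c on that scale, the false path is cd.

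| c = d | cd/(1 + c²) | cd |
|---|---|---|
| 0.3 | 0.09/1.09 = 0.08 | 0.09 |
| 0.5 | 0.25/1.25 = 0.20 | 0.25 |
| 0.7 | 0.49/1.49 = 0.33 | 0.49 |

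**4. Risk-ratio scale (assumed)**

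Suppose the true total risk ratio is 0.85 and a share s of the log effect runs through drivers adjusted after entry, with no shared unmeasured cause. The adjusted ratio is 0.85^(1 - s): 0.89, 0.92 and 0.95 for s = 0.3, 0.5 and 0.7.

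**The case against.** The case against a broad criticism is substantial, and most of it stands.

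- **Timing.** A reader might infer that the plan adjusts for drivers measured after BFP entry and so estimates neither the total nor the indirect effect. The article does not say this. The covariate list carries no timing, and the one explicit rule, for the propensity score, points to values before treatment. Table 1 labels the socioeconomic source as the cohort baseline. Against this, income instability may need repeated readings, and Study innovation promises to follow changes in living conditions. Timing is unfixed; it is not fixed wrongly.
- **The four mechanisms.** A reader might infer that these are adjusted away. They are absent from the covariate list, and they are analysed as outcomes of BFP and as nodes with estimated paths.
- **Total effects.** Aim 1 plans these separately with its own matching list, so the Aim 2/3 covariates need not touch them.
- **Model choice.** One might say that fit decides the direction of the arrows. The text is tentative, the models follow Fig 1, and Fig 1 is not available here, so whether reversed paths are candidates cannot be checked.
- **Microsimulation.** Step 2 draws on the retrospective analyses in general and does not single out the structural equation models. It does not follow that its inputs would be wrong.
- **Level of detail.** The choice of mediation estimand and of models for rare outcomes can be left to a fuller document.

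None of this rescues the sentence on mediators. It is a wrong statement rather than an omitted detail, and it does not depend on timing. Nor does it resolve the double role of income.

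**Conclusion.** The point holds in a limited form, as a should-fix. The description of mediators as representations of confounders is incorrect, and so is the claim that calculated path coefficients suffice for precise mediator effects. The claim fails under unmeasured mediator-outcome confounding, or when a mediator-outcome confounder is itself changed by BFP. Separately, social drivers, income most clearly, are both hypothesised route and covariate in the same analyses with no stated timing. Bias in the total and indirect effects from that adjustment is conditional on measurement after BFP entry.

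The sizes above are illustrative and rest wholly on assumed coefficients, an assumed risk ratio of 0.85 and linear or log-linear models without interaction. They show that the bias can be material, not how large it will be here. Shrinkage toward the null is what these settings give; it is not a general rule, because conditioning on a post-entry driver that shares an unmeasured cause with the outcome can bias either way.

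**What to change.** 1. Delete or correct the sentence on mediators. Say that a mediator is affected by BFP and in turn affects the outcome, and that path coefficients have a causal reading only under stated assumptions.
2. Classify each variable in advance as confounder, mediator or moderator, income and the other listed drivers included.
3. Restrict adjustment covariates to values measured at or before BFP entry, or at the matched index date for non-beneficiaries.
4. State the identification assumptions for the Aim 2 mediated effects. These should cover unmeasured mediator-outcome confounding and any mediator-outcome confounder that BFP changes, since step 3 does not remove that second problem.
5. Report a sensitivity analysis for unmeasured mediator-outcome confounding.
6. Use model fit as a diagnostic and not as evidence of a variable's causal role.

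The cost is revised wording, some programming and extra analysis, and more cautious mediation claims. No new data are required.
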